### Economic data analysis

The primary economic evaluation will explore the relationship between cost and outcome for the three treatments for AOMd (immediate topically, delayed orally and immediately administered oral antibiotics) from an NHS perspective at 14 days post randomisation. This will take the form of a simple comparison of NHS costs and outcomes over a period of 2 weeks from randomisation.

A secondary cost analysis will evaluate the difference in NHS secondary care costs between the trial arms for the 3 months following randomisation.

All resources will be valued using unit costs from established sources. These will include Unit Costs of Health and Social Care [25] for primary and community care, NHS Reference Costs [26] for hospital care and the BNFC [27] for prescribed medication.

Differences in NHS resources and costs between the arms will be analysed initially using Ordinary Least Squares (OLS) regression. The distribution of residuals from the regression models will then be examined and a decision will be made as to whether OLS is appropriate or another type of regression model should be considered (e.g. Generalised Linear Models (GLM)).

A cost-consequence analysis will then be conducted in which the costs to the NHS of the three treatments at 14 days post randomisation will be compared with the primary clinical outcome. Areas of uncertainty in assumptions will be subjected to sensitivity analyses to test the robustness of the results.

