## Background and rationale

Acute otitis media (AOM) is important to children, parents and the National Health Service (NHS). Firstly, the infection causes pain and distress to the child, disrupting sleep and family routines. In around 15% of cases, a rise in middle-ear pressure and/or inflammation weakening the tympanic membrane results in it bursting, discharging pus from the middle ear as a discharge (otorrhoea) [1]. Children with AOM and discharge (AOMd) have similar levels of pain and are more unwell at presentation than children with AOM [2, 3]. Moreover, children with AOMd have a worse prognosis, and higher rates of pain at 1 week, as reported by parents (carers), repeat AOM episodes and hearing problems at 3 months [2]. Estimates of parental costs (travel, over the counter (OTC) medicines and lost earnings) vary [4–6], with even the lowest suggesting £4 million in England and Wales per annum.

Over 90% of UK parents attend primary care health services for each episode of AOMd [7], with over 150,000 general practitioner (GP) consultations for AOMd in England and Wales per annum at a cost to the NHS of over £3 million [4, 5], which is more than for any other common symptom of acute infection.

More children with AOM and AOMd receive an orally administered antibiotic in the UK [8] and the United States [9] than for any other respiratory infection, with three quarters of GPs prescribing orally administered antibiotics to at least 80% of children diagnosed as such [10, 11]. Our 2015 audit, including 33 GP practices and 56,251 children, confirmed that immediate orally administered antibiotics is usual care for AOMd: 88% were given orally administered antibiotics of which 97% were given immediately.

There is strong evidence that children with AOMd benefit from immediate orally administered antibiotics. The number needed to treat with antibiotics is three to reduce the proportion of children with pain and/or fever at 3–7 days compared with placebo/no treatment [3]. The National Institute for Health and Care Excellence (NICE), therefore, recommends that immediate antibiotics should be considered [12]. Orally administered antibiotics do, however, also cause side effects, are associated with subsequent eczema and hay fever [13] and with population [14] and patient-level [15] antimicrobial resistance.

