#### Patient-reported outcomes

All parents/legal guardians are asked to complete a daily SRQ recording the symptoms identified by parents/legal guardians as important. The SRQ will be provided in electronic format via the TRANSFoRm app or in a paper version. The SRQ will provide a daily record of symptom burden and will be completed up to 14 days. The primary outcome will be collected using the SRQ with research nurse telephone calls on days 1, 3, 7, 10 and 14.

On day-7 and day-14 telephone calls, information on the use of healthcare resources including information about primary care contacts, use of 111, walk-in centres and hospital services will be obtained.

At month 3, use of hospital services will be collected by review of the patients’ EHR.

The final questionnaire will be sent 3 months after randomisation either electronically (web or iOS/Android app) via the TRANSFoRm platform or paper questionnaire. The questionnaire will ask about parent/legal guardian-reported hearing loss at 3 months as measured using the OM6 [22] questionnaire.

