### Economic data collection

The economic evaluation will explore the relationship between cost and outcomes for the three proposed methods of treating AOMd. This will be done for the short term (14 days) to assess the cost-effectiveness of immediate topically or delayed orally administered antibiotics compared with immediate orally administered antibiotics, and the longer term (3 months) in order to capture the effects of any recurrence of symptoms and lasting side effects. The perspectives will be from the NHS, parents/carers, and lost productivity due to time off work and school.

During the trial, participants will complete a symptom diary which will record any use of healthcare resources not available from the GP notes (for example, community care and the use of 111 and walk-in centres) and non-healthcare costs incurred by parents/carers during the first 14 days such as travel costs, purchase of over-the-counter medications, childcare and loss of earnings due to time off work. We will also ask about time off nursery/school.

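### The 3-month cost analysis is meant to reflect recurrence but covers secondary care only, so GP-managed recurrences after day 14 carry no cost in it

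*Protocol article*

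**What the plan says.** Four sections of the protocol article bear on this.

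- **Economic data collection** gives the reason for looking beyond 14 days: "the longer term (3 months) in order to capture the effects of any recurrence of symptoms and lasting side effects".
- **Economic data analysis** describes one 3-month cost analysis: "A secondary cost analysis will evaluate the difference in NHS secondary care costs between the trial arms for the 3 months following randomisation". The primary economic evaluation and the cost-consequence analysis are both set at 14 days from an NHS perspective. The same section names unit-cost sources for primary and community care, hospital care and prescribed medication.
- **Patient-reported outcomes** sets out when resource use is gathered. Primary-care use is asked about early: "On day-7 and day-14 telephone calls, information on the use of healthcare resources including information about primary care contacts". The later item is narrower: "At month 3, use of hospital services will be collected by review of the patients’ EHR".
- **Background and rationale** says where these episodes are seen: "Over 90% of UK parents attend primary care health services for each episode of AOMd". It puts the volume and cost at "with over 150,000 general practitioner (GP) consultations for AOMd in England and Wales per annum", costing the NHS more than £3 million.

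Repeat AOM and AOMd episodes at 3 months are a secondary outcome under Outcome measures. Nothing in the article says that those episodes are costed.

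**The concern.** The stated purpose and the planned analysis do not match. A child whose ear discharges again in week 6, who sees the GP and receives another antibiotic course, is the kind of case the longer horizon is said to be for. Under the 3-month analysis as worded, that child contributes nothing unless a hospital is involved.

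The article gives reasons to expect that recurrence could differ by arm. It makes recurrence at 3 months a secondary objective, and it reports that in children with grommets topical antibiotics reduced AOM recurrence compared with oral ones. Any such difference, in either direction, would lose its primary-care part in the 3-month cost comparison. Repeat antibiotic courses would be left out too, although reducing systemic antibiotic use is the reason for the trial. A reader told that the 3-month costs reflect recurrence would take the result to mean more than it does.

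**Working it through.** **Step 1: compare purpose, data and analysis.**

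| Element | Scope in the article |
|---|---|
| Purpose of the 3-month horizon | Recurrence and lasting side effects |
| Primary-care contacts | Asked about on the day-7 and day-14 calls |
| Family costs in the diary | "non-healthcare costs incurred by parents/carers during the first 14 days" |
| Resource item named at month 3 | Hospital services, from the record |
| 3-month cost analysis | NHS secondary care |
| Where AOMd episodes are seen | Primary care, for over 90% |

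The gap is day 15 to month 3. Primary-care use up to day 14 belongs to the 14-day evaluation and is not in question.

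**Step 2: primary-care cost per AOMd recurrence.** The article states no figure for this, so there is none to reproduce. Inputs, from the Background: over £3 million, over 150,000 consultations, over 90% attendance.

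- Cost per consultation = £3,000,000 / 150,000 = about £20.
- Cost per recurrence = 0.9 × £20 = about £18, before prescriptions, taking one consultation per attended episode.

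Both parts of the £20 ratio are given only as more than the stated figure, so £20 is approximate and not a bound.

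**Step 3: effect on a comparison between arms (assumed differences).** Missed consultation cost per child = difference in recurrence × £18.

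- 5 points: 0.05 × £18 = £0.90
- 10 points: 0.10 × £18 = £1.80
- 20 points: 0.20 × £18 = £3.60

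The article gives no expected difference in recurrence.

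**Step 4: can the share of money missed be found?** Let h be the proportion of recurrences that use hospital care and C the cost of each such use. Share captured by hospital-only costing = hC / (hC + 18), before prescriptions. The article gives neither h nor C, so all values below are assumptions.

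| h | C | hC | Share captured |
|---|---|---|---|
| 0.5% | £200 | £1 | 1/19 = 5% |
| 1% | £500 | £5 | 5/23 = 22% |
| 1% | £1,000 | £10 | 10/28 = 36% |
| 2% | £1,000 | £20 | 20/38 = 53% |
| 5% | £1,000 | £50 | 50/68 = 74% |

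More than half of this cost is missed only when hC is below £18. The documents do not say which side of that line the trial falls on.

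**The case against.** The strongest reply is that the 3-month analysis is plainly labelled as secondary care and is a secondary analysis. The article's listed cost objective is short-term, and the main economic results are at 14 days. Recurrence is also compared between arms as an outcome in its own right, so an arm with more repeat episodes would not go unnoticed. The per-child sums are small, and the Trial status section reports only 22 children recruited, so the 3-month comparison will be imprecise whatever it includes. All of this stands, and it limits the importance of the point. It does not remove the mismatch, because the label contradicts the purpose stated for the same horizon.

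Three stronger readings are tempting, and the documents do not support them.

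- *Most of the cost of recurrence is missed.* The article supports this for AOMd episodes and their primary-care contacts, not for money, as Step 4 shows. The attendance figure is also for AOMd, while the recurrence outcome includes AOM without discharge.
- *Primary-care data after day 14 are not collected at all.* Economic data collection treats the GP notes as a source of resource use, and the Abstract mentions routine NHS follow-up data from the platform. Neither shows that GP contacts are extracted to month 3, but in a condensed article they make a flat denial too strong. The firm restriction is on what is costed.
- *The recurrence outcome is poorly ascertained and should rest on coded GP episodes.* Trial design says secondary outcomes at 3 months come by questionnaire, and the details may lie in the full protocol. Coded episodes would miss children not taken to primary care, and in an open trial re-consultation can itself be influenced by allocation. The choice of source is a preference, not a correction.

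Nor can the point be set aside as detail left to a fuller document. The article is not silent: it limits both the month-3 item and the 3-month analysis to hospital or secondary care.

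**Conclusion.** The point holds as an inconsistency between the stated purpose of the 3-month economic horizon and the scope of the analysis meant to serve it. Followed as written, the 3-month comparison assigns no cost to primary-care management of recurrences from day 15 onward. For AOMd, that means omitting about £18 in consultations per recurrence, plus prescriptions. This rests on the article's national figures and on the attendance rate for AOMd episodes applying to recurrences. The effect on any difference between arms depends on a recurrence difference that the article does not give, and the share of total recurrence cost lost cannot be determined. The 14-day primary economic evaluation is unaffected. The point is worth correcting but does not threaten the trial's main conclusions.

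**What to change.** Extend the month-3 review of the same GP record to primary-care contacts and antibiotic prescriptions for AOM or AOMd from day 15 to month 3. Reword the 3-month analysis as one of NHS primary and secondary care costs, valued with the unit-cost sources that Economic data analysis already names.

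The cost is modest extra extraction and costing work. The record is already being reviewed, and the trial platform is integrated with it. With recruitment reported as closed, the extraction would be retrospective, so the team should confirm that consent and approvals cover it; the article does not settle that.

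If the extraction is not done, amend Economic data collection so that the 3-month analysis is described as a comparison of secondary care costs and is not said to capture the effects of recurrence. That costs only a change of wording. No change to the source of the recurrence outcome is needed.

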### Qualitative data analysis

Interview transcripts will be imported into NVivo 12 qualitative data analysis software. Analysis will begin shortly after data collection starts and will be ongoing and iterative – informing further data collection and identifying changes needed to the topic guide. Thematic analysis [28], utilising a data-driven inductive approach, will be used to identify and analyse patterns and themes of particular salience for participants and across the dataset using constant-comparison techniques [29, 30]. A subset of transcripts will be independently double-coded by members of the team (CC and JH); any discrepancies will be discussed within the team and resolved to achieve coding consensus and maximal rigour.

### Blinding

Once the allocation is revealed, neither clinicians nor the child participant or their parent/legal guardian will remain blind to their allocated treatment. Codes will be assigned to the database, which will preserve blinding of study personnel. The senior statistician will remain blind to knowledge of which treatment is represented by each treatment code until the final results have been shared with the Data Monitoring Committee (DMC). Emergency unblinding will not be necessary in this trial since it is an open study.

### Dissemination

We will publish the trial results in peer-reviewed journals and present at national and international meetings. With the assistance of our collaborators and PPI we will disseminate the study findings to an international audience. All participants will be offered a lay summary of the main findings of the study.

## Discussion

This article outlines a pragmatic, three-arm, individually randomised trial, which aims to recruit from 175 GP practices across the UK. The aim is to establish evidence for the non-inferiority of: (1) immediate topical ear drops, ciprofloxacin 0.3%; (2) delayed orally administered amoxicillin (clarithromycin) or (3) immediate orally administered amoxicillin (clarithromycin). The non-inferiority will be based on time to resolution of all significant symptoms. Secondary outcomes will include cost-effectiveness, duration of moderately bad or worse symptoms and repeat AOMd episodes.

Recruitment of 399 children with AOMd over a 22-month period presented challenges around the design of the REST study. Only two to three patients’ children were expected to present at each GP practice over the 22-month recruitment period, requiring at least 175 GP practices to take part in the study.

In order to make this study feasible we needed to consider novel and streamline mechanism to facilitate greenlighting of sites, training of site staff, identification of eligible participants and the collection of high-quality data.

We employed several different strategies in order to address these elements of the study, these included:
Development of a remote training platform to deliver REST study training to GPs and staff at recruiting practicesA light-touch Green Light Process (GLP), maximising the number of staff at the GP practices able to recruit to the REST study by providing quick and accessible study-specific training

We used the TRANSFoRm electronic platform, (integrates into the health records) to automatically create a pop-up alert to the clinician when an eligible patient presents. The system automatically checked the participant’s eligibility and part-filled the study eCRFs reducing the efforts of the clinician to record study data.

### Trial status

Currently, 50 SystmOne GP practices have been greenlighted across seven CRN regions in the UK. The first child was recruited to the study on 5 April 2019 with recruitment currently ongoing. A total of 22 children were recruited to the REST study, with recruitment being closed on 31 May 2020.

Protocol: Version 7.0, 31 October 2018

Open to recruitment: 7 April 2019

Planned recruitment closure date: 31 March 2020

## Data Availability

The datasets analysed during the current study will be available from the corresponding author on reasonable request.

## Abbreviations

AOMd: Acute otitis media with discharge
AE: Adverse event
CI: Chief investigator
CRF: Case Report Form
EHR: Electronic Health Record
GP: General practitioner
NHS: National Health Service
NICE: National Institute of Health and Social Care
PI: Principal investigator
TMG: Trial Management Group
TSC: Trial Steering Committee
DMC: Data Monitoring Committee
